#### Withdrawal criteria 

The Withdrawal criteria will be the following: (1) those who failed to follow the trial protocol treatment; (2) those who do not wish to continue in the trial; (3) those whose condition has worsened after the start of the trial or who have had a serious adverse event that makes continuation of the trial inadvisable.

### Who will take informed consent? {26a}

Based on the above criteria, to confirm that a patient undergoing TKA has been screened for eligibility to participate in this study, the treatment team has assessed the patient as eligible, and the surgeon will complete the initial study information for the patient. The patient is invited to meet with the investigator and physician to discuss any remaining questions and sign an informed consent form.

The Informed Consent Form is provided as Supplementary File S1. These templates cover study purpose/procedures, risks and benefits (including rTMS-related risks), alternatives, confidentiality and data handling, biospecimen use and destruction, compensation/contacts, and the voluntary right to withdraw without affecting care.

### Additional consent provisions for collection and use of participant data and biological specimens {26b}

In this study, participants’ biospecimens will be collected and patients will be informed of the purpose of biospecimen collection and possible privacy risks, and consent will be obtained from the participants.

## Interventions

### Explanation for the choice of comparators {6b}

The control group received standardized perioperative management.

### Intervention description {11a}

#### Control group

The control group will be subjected to standardized perioperative management. Specific measures are as follows: (1) Preoperative phase: patients will undergo a standardized perioperative pathway comprising functional assessment to inform care and prehabilitation focusing on quadriceps-strengthening exercises; pharmacological venous thromboembolism (VTE) prophylaxis will be administered as per institutional protocol. All eligibility screening is detailed under the “Eligibility criteria {10}” and “Recruitment {15}” sections. (2) Intraoperative phase: the procedure was performed under spinal-epidural anesthesia. A medial parapatellar approach was utilized for component implantation. A tourniquet, inflated to 250–300 mm Hg, and intravenous tranexamic acid (15 mg/kg) were employed to reduce perioperative blood loss. (3) Postoperative phase: pain management involved a multimodal regimen incorporating femoral nerve blocks and oral analgesics (acetaminophen/celecoxib). VTE prophylaxis was continued with intermittent pneumatic compression and rivaroxaban (10 mg/day). Early mobilization was enforced, with ambulation commencing on the first postoperative day. Patients were monitored daily for complications, including surgical site infection, VTE, and neurovascular injury.

#### Active rTMS group

The active rTMS group will be given active rTMS treatment based on standardized perioperative management. Active rTMS will be delivered using a magnetic stimulator (YRD-CCY-1, YIRUIDE Medical Equipment, Wuhan, China) with a figure-of-eight 70-mm coil positioned tangential to the scalp over the left dorsolateral prefrontal cortex (DLPFC; 10–20 system F3). Stimulation will be applied at 10 Hz in 5-s trains with 25-s inter-train intervals, 2000 pulses per session, at an intensity of 100% of the resting motor threshold (RMT). RMT will be defined as the lowest stimulator output that elicits motor-evoked potentials (MEPs) ≥ 50 μV in the relaxed right abductor pollicis brevis in ≥ 5 of 10 trials. Sessions will be delivered once daily for five consecutive pre-operative days. No post-operative rTMS will be delivered in this protocol; surgery is scheduled within 24–48 h after the final pre-operative session. Participants will be continuously monitored; if intolerable local discomfort occurs, stimulation will be stopped immediately and documented.

Rationale for stimulation site: The left dorsolateral prefrontal cortex (DLPFC) is a hub of executive-control and working-memory networks implicated in early postoperative cognition. Against the peri-operative neuroinflammatory background relevant to POCD (e.g., IL-1β, IL-6, TNF-α, HMGB1), prefrontal neuromodulation offers a biologically plausible route to support cognition and modulate inflammatory signaling. Accordingly, the left DLPFC (F3) was selected as the stimulation target.

#### Sham rTMS group

The sham rTMS group will be given sham rTMS treatment based on standardized perioperative management. The stimulation site, stimulation parameters, and treatment schedule of the sham rTMS treatment will all be the same as the active rTMS group, and the patient will be able to hear the sound of the magnetic stimulator. However, the coil will be placed perpendicular to the skull surface.

### Criteria for discontinuing or modifying allocated interventions {11b}

Participant-level criteria and actions: An rTMS/sham session will be interrupted or discontinued if any of the following occur during or immediately after stimulation: (1) intolerable scalp discomfort or pain despite repositioning; (2) vasovagal syncope or pre-syncope; (3) sustained hypertension (> 180/110 mmHg), tachycardia (> 130 bpm) or clinically significant arrhythmia; (4) new focal neurological symptoms/signs; (5) any seizure; (6) coil-related skin heating/burn; or (7) persistent severe headache not relieved by simple analgesia, or any other event judged clinically significant and related to the procedure by the investigator. The session will be stopped, clinical care provided, and the event documented and reported per the Harms procedures (see {22}). Resumption of stimulation at a reduced intensity and/or fewer trains may be considered after resolution of symptoms at the investigator’s discretion. Occurrence of a seizure or any unanticipated serious adverse device effect will lead to permanent discontinuation of rTMS for that participant. Participants may also withdraw from the intervention at any time; unless consent is withdrawn, they will remain in outcome follow-up (intention-to-treat).

Trial-level pausing or termination: Decisions to pause, modify, or terminate the trial will be guided by the independent DSMB according to pre-specified safety triggers and overall safety review (see Interim analyses and stopping guidelines {21b} and Harms {22}). Illustrative triggers include: any definite device-related seizure; ≥ 2 rTMS-related SAEs or an rTMS-related SAE rate > 5% and exceeding the sham arm by ≥ 5 percentage points; any unanticipated serious adverse device effect; or a clear excess of all-cause SAEs in the active rTMS arm at a scheduled review. The DSMB will issue recommendations to the TSC and Sponsor/PI; final operational decisions will be made by the Sponsor/PI upon TSC advice.

### Strategies to improve adherence to interventions {11c}

The rTMS treatment program is known for its high degree of flexibility and safety and can respond to and adapt to the individual needs of the patient, thus ensuring a very high program compliance rate. The entire rTMS treatment process will be carried out under the strict supervision of our hospital’s experienced and professional rehabilitation therapists to ensure the professionalism, safety, and effectiveness of the treatment process.

### Relevant concomitant care permitted or prohibited during the trial {11d}

Perioperative use of medications that substantially affect cognition (e.g., benzodiazepine sleep aids, anticholinergic antiemetics/antihistamines, and high-dose antipsychotics for non-delirium indications) will be prohibited unless clinically indispensable and the expected benefits outweigh the risks to study validity. The anesthesia and surgical teams will follow a standardized, enhanced recovery after surgery (ERAS)-consistent pathway to minimize such exposure; where antiemetic or sedative and analgesic therapy is required, non-anticholinergic alternatives (e.g., ondansetron) and opioid-sparing strategies will be preferred; meperidine (pethidine) will be avoided. Any rescue use of prohibited/limited agents will be prospectively recorded (drug, dose, frequency, duration, timing, indication) as a protocol deviation without excluding the participant from intention-to-treat analyses. Medication exposure will be captured during hospitalization and at discharge. Quantitative exposure metrics—including total opioid burden expressed as morphine milligram equivalents (MME) and a composite psychotropic medication score—will be incorporated as covariates in the primary regression models to adjust for potential confounding. A prespecified sensitivity analysis will exclude participants with extreme exposure to potentially confounding medications to assess robustness.

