### Outcomes {12}

#### Primary outcome (five-element specification)

Domain: POCD.

Specific measurement: MoCA administered at four scheduled assessments (preoperative day six, preoperative day one (baseline), postoperative day three, postoperative day seven) by a trained, blinded assessor.

Metric: Binary classification of POCD at each postoperative assessment. POCD is defined a priori as a ≥ 20% decline from baseline in ≥ 2 MoCA items (Newman criteria) [17].

Method of aggregation: The group-level proportion with POCD at postoperative day seven (primary time point); between-group effect expressed as risk ratio with 95% CI from a log-binomial model (logistic regression if non-convergent), adjusted for age, sex, education, and baseline MoCA.

Time point: postoperative day seven (primary); postoperative day three analyzed as supportive.

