### Plans to promote participant retention and complete follow-up {18b}

During recruitment, participants will receive comprehensive information on study procedures, requirements, and the importance of completing follow-up. Participants may discontinue rTMS at any time without obligation to provide a reason; withdrawal from the intervention does not constitute withdrawal from follow-up unless consent is revoked. To enhance retention and minimize missing data, we will use multi-modal reminders (phone, text, and written), provide reminders to complete questionnaires at each study visit, offer flexible assessment windows around each time point, and, where feasible, arrange transport assistance. All contact attempts and outcomes will be prospectively logged.

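### Medication exposure is recorded to discharge, not to the day-seven test, so for anyone discharged earlier the totals miss the last days before the primary MoCA and vary with length of stay

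*Protocol article*

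**What the plan says.** All references are to the protocol article.

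- **Capture window.** Section {11d}, on concomitant care, states: "Medication exposure will be captured during hospitalization and at discharge".
- **Primary endpoint.** Outcomes {12} gives: "Time point: postoperative day seven (primary); postoperative day three analyzed as supportive". Section {20a} uses the same day.
- **Use of the exposure data.** Section {11d} says the quantitative metrics, an opioid total in morphine milligram equivalents (MME) and a composite psychotropic score, "will be incorporated as covariates in the primary regression models to adjust for potential confounding". It adds: "A prespecified sensitivity analysis will exclude participants with extreme exposure to potentially confounding medications to assess robustness".
- **A second record.** The same section says: "Any rescue use of prohibited/limited agents will be prospectively recorded (drug, dose, frequency, duration, timing, indication) as a protocol deviation". It gives no end date for this record and does not say how use at home would be found.
- **Hints on length of stay.** No section states a discharge day or requires a stay to day seven. The surgical and anesthesia teams "will follow a standardized, enhanced recovery after surgery (ERAS)-consistent pathway to minimize such exposure". The control-group description says: "Early mobilization was enforced, with ambulation commencing on the first postoperative day". The retention plan {18b} will "offer flexible assessment windows around each time point, and, where feasible, arrange transport assistance".
- **POCD and length of stay.** Background and rationale {6a} lists longer hospitalization among the possible consequences of POCD.

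**The concern.** The protocol restricts certain drugs because they affect cognition, then measures cognition on day seven. The exposure most relevant to that measurement is what the patient took shortly before it. Discharge is a different event from the day-seven test, and it falls on a different day for different patients.

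Two things are at stake. First, for a patient discharged early, opioid use in the days nearest the test has no stated route into the data. Second, a total that stops at discharge covers a different number of days in each patient. If POCD prolongs the stay, as the Background suggests it may, patients with POCD are observed for longer and can accumulate higher recorded totals. An analysis that drops patients with extreme totals could then remove POCD cases preferentially. The limitations paragraph of the Discussion relies on prospective recording and covariate adjustment as its answer to variation in analgesic and antiemetic regimens, so the quality of this measure matters to the trial's own argument.

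**Working it through.** The plan gives no figure to reproduce here. The check compares the texts and adds a small illustration.

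**Step 1: the two windows.** Capture ends at discharge ({11d}). The primary test is on day seven ({12}, {20a}). No section links them, and none describes a medication record between discharge and the day-seven MoCA.

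**Step 2: what each record covers after discharge.**

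| Exposure | Stated record | After discharge |
|---|---|---|
| Opioids generally (MME) | Hospital stay and discharge | No stated capture |
| Prohibited or limited agents | Rescue-use record with timing and duration | No stated end date, no stated method |

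The opioid part is the firmer gap, because opioids in general are not among the prohibited examples in {11d}.

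**Step 3: size of the gap for one patient.** Let *d* be the postoperative day of discharge. It is an assumption, because the documents give none.

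Uncaptured days = max(0, 7 − *d*); share = uncaptured days / 7.

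| Assumed *d* | Uncaptured days | Share of seven days |
|---|---|---|
| 3 | 7 − 3 = 4 | 4/7 = 57% |
| 4 | 7 − 4 = 3 | 3/7 = 43% |
| 5 | 7 − 5 = 2 | 2/7 = 29% |
| 6 | 7 − 6 = 1 | 1/7 = 14% |
| 7 or later | 0 | 0% |

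These are shares of days, not of drug intake. The proportion of patients affected cannot be computed from the documents.

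**Step 4: comparability of totals.** Take two patients with the same true intake and, purely for illustration, a constant daily amount *c*. Discharge on day three records 3*c*, and a stay to day seven records 7*c*. The ratio is 7/3 ≈ 2.3, with no difference in actual use. Intake that falls over the week would make the ratio smaller. In the other direction, the wording sets no stop at day seven, so a longer stay could add exposure that came after the primary test.

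**Step 5: where the totals go.** Section {11d} puts them into the primary models and uses them to define an exclusion. Sections {12} and {20a} list age, sex, education and baseline MoCA as the primary adjustment set, without exposure metrics. The covariate statements therefore disagree, and the extra covariates in {11d} are measured after randomization.

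**The case against.** The strongest case against the point has four parts.

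*No early discharge is documented.* The enhanced recovery pathway is cited as a means of limiting drug exposure, walking on day one fixes no discharge day, and reminders and transport help apply to every time point, two of which are preoperative. This stands: early discharge is plausible on the text but not established.

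*Restricted drugs have their own record.* A reader might infer that sedatives taken at home are simply missed. The documents do not support that. Rescue use of prohibited or limited agents is to be recorded with timing and duration, and no end at discharge is stated. The record taken at discharge may also list prescriptions. What remains is that no method for detecting home use is described, that a prescription does not show intake, and that opioids in general lie outside the listed prohibited examples.

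*Heavy exposure near day seven may be uncommon.* Patients who cannot stop sedative-hypnotics or anticholinergic drugs at least 4 weeks before baseline are excluded, the named oral analgesics are acetaminophen and celecoxib, and opioid-sparing care is preferred. This lowers the likely impact without closing the gap.

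*The detail may sit in the full protocol or eCRF.* It may. But the article does more than stay silent: it states a capture window and ties it to discharge. If a day-seven record already exists, one corrected sentence settles that part.

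**Conclusion.** The point holds as a modest, inexpensive improvement. The stated capture window is anchored to discharge, while the endpoint it should serve is anchored to day seven. For any participant discharged before day seven, opioid use up to the test has no stated capture. Exposure totals then cover unequal periods, so the totals and the extreme-exposure exclusion are not comparable across patients and may depend on the outcome.

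The size is conditional. With discharge assumed on day three to six, 57% to 14% of the seven postoperative days go uncaptured for that patient; with a stay to day seven the loss is nil. Dependence on the outcome rests on the protocol's own premise that POCD may lengthen the stay.

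A reader might go further and infer that the primary result is biased. The documents do not support that: unrecorded home use does not in itself bias a randomized intention-to-treat comparison that adjusts only for the baseline covariates in {12} and {20a}. The effect is on reporting by arm and on the sensitivity analysis. It reaches the primary estimate only if the {11d} statement about covariates is followed, which is why that statement needs to be reconciled.

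**What to change.** 1. Replace the capture sentence in {11d} with: *Medication exposure will be captured from surgery through the postoperative day seven assessment, irrespective of discharge date.*
2. At the existing day-three and day-seven visits, record any opioid or restricted agent taken in the 24 hours before testing (drug, dose, time). A cumulative total cannot show whether the patient was medicated when tested; this item can.
3. Compute the MME total and psychotropic score over the same fixed windows for every participant (surgery to day three, surgery to day seven). Use them for reporting by arm and for the extreme-exposure sensitivity analysis.
4. Reconcile {11d} with {12} and {20a} on whether these post-randomization metrics enter the primary models, so that one covariate list stands.

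The cost is a few eCRF fields and a short question at visits already scheduled. Post-discharge use will be self-reported and so less reliable than ward records, but that is better than no record. The change touches no drug, dose or clinical rule. Enrollment was under way when the article was written, and intake not asked about at the time is hard to recover, so the change is worth making promptly. Participants already past day seven should be identified as having discharge-limited data.

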### Statistical methods

#### Statistical methods for primary and secondary outcomes {20a}

Analyses will follow intention-to-treat. Primary endpoint (POCD at postoperative day seven) will be compared between groups using log-binomial regression to estimate risk ratios (95% CI), adjusted for age, sex, education, and baseline MoCA; logistic regression will be used if convergence issues arise. A supportive analysis will model POCD trajectories at postoperative day three and postoperative day seven using generalized estimating equations with a log link.

Continuous secondary outcomes (MoCA total, DST, DSST, TMT, DSR) will be analyzed using linear mixed-effects models (fixed effects for group, time, and group × time; random intercept for participant), adjusting for baseline. For TMT, if residuals are markedly non-normal, we will report median (IQR) and between-group Hodges–Lehmann differences as pre-specified sensitivity analyses. Inflammatory markers will be log-transformed and analyzed using ANCOVA at each post-op time point with baseline adjustment; results will be back-transformed as geometric mean ratios (95% CI). Missing data will be handled under a missing-at-random assumption via maximum likelihood; multiple imputation (*m* = 20) will be a sensitivity analysis. Multiplicity across secondary outcomes will be controlled by the Benjamini–Hochberg procedure (false discovery rate 5%).

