The study also has limitations. It is single-center with a modest sample size and a short follow-up window, which may limit external validity and preclude conclusions about durability. Although perioperative care is standardized, residual confounding from unavoidable variations in analgesic and antiemetic regimens cannot be fully excluded despite prospective recording and covariate adjustment. In addition, there is no field-wide consensus on optimal rTMS parameters for postoperative cognition, including coil target, trains, pulses per session, and session frequency; our protocol tests one biologically informed option but not the full parameter space.

Future work should be concrete and hypothesis-driven. If the present results are positive, a multi-center confirmatory trial should (1) optimise dose and schedule (train number, intensity, timing relative to surgery), (2) extend follow-up to 1–3 months to assess durability and patient-centered outcomes, and (3) incorporate mediation analyses to test whether cytokine changes statistically explain cognitive benefit. Subgroup analyses by age or baseline cognitive reserve may clarify heterogeneity of treatment effect, and optional mechanistic sub-studies using EEG or functional neuroimaging could validate network engagement. If results are null, parameter refinement (targeting, intensity, timing) and outcome sensitivity should be interrogated before deprioritizing rTMS for POCD prevention.

In conclusion, if rTMS meaningfully improves early postoperative cognition in older adults after TKA, it would support the development of non-pharmacological, neuromodulation-based adjuncts within enhanced recovery pathways to mitigate or even arrest postoperative cognitive decline.

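### The primary model is specified in two conflicting ways, and one of them adjusts for drug exposure arising largely after randomisation, which can bias the intention-to-treat risk ratio

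*Protocol article*

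**What the plan says.** The primary outcome specification in Outcomes {12} defines the between-group effect on POCD at postoperative day seven as a risk ratio from a log-binomial model, "adjusted for age, sex, education, and baseline MoCA". Statistical methods {20a} repeats this: "log-binomial regression to estimate risk ratios (95% CI), adjusted for age, sex, education, and baseline MoCA". Neither section has a medication term. {20a} also states the analysis principle: "Analyses will follow intention-to-treat".

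The concomitant-care section {11d} names two exposure metrics, "total opioid burden expressed as morphine milligram equivalents (MME) and a composite psychotropic medication score", and says that they "will be incorporated as covariates in the primary regression models to adjust for potential confounding". On timing it says: "Medication exposure will be captured during hospitalization and at discharge". It adds a prespecified sensitivity analysis that leaves out participants with extreme exposure.

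On the intervention, the active rTMS section says: "Sessions will be delivered once daily for five consecutive pre-operative days". Surgery follows within 24 to 48 hours of the last session.

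The Discussion returns to the subject among the limitations: "residual confounding from unavoidable variations in analgesic and antiemetic regimens cannot be fully excluded despite prospective recording and covariate adjustment". The {11d} statement is therefore not an isolated phrase.

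**The concern.** There are two faults. First, the protocol fixes the primary model more than once and the versions disagree. If {11d} is read as adding to the list in {12} and {20a}, then those two sections misstate the primary model. If it is not, {11d} does. Either way two candidate primary estimates and p-values exist, and the choice between them could be made after the data are seen.

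Second, the reason given for the extra terms does not apply. Randomisation deals with confounding by factors present before allocation. Drug exposure that arises afterwards cannot influence which arm a participant was assigned to. It can lie on the path from rTMS to cognition, for example through pain and analgesic use, or share causes with POCD such as frailty, pain or acute confusion. Conditioning on a mediator removes part of the effect being estimated. Conditioning on a variable that is affected by treatment and shares causes with the outcome can create an apparent effect where there is none. In both cases the adjusted risk ratio is no longer the total effect of allocation, which is what intention-to-treat promises.

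**Working it through.** **Text comparison.**

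| Section | Covariates in the primary model | Medication terms |
|---|---|---|
| {11d} | Not listed in full | MME and psychotropic score |
| {12} | Age, sex, education, baseline MoCA | None |
| {20a} | Age, sex, education, baseline MoCA | None |
| Discussion, limitations | Not listed | Refers to covariate adjustment for analgesic and antiemetic variation |

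No section reconciles these or ranks the medication-adjusted model as secondary.

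**Timing.** Consent precedes allocation (Recruitment {15}), and allocation must precede the first active or sham session. The sessions fill five preoperative days and surgery follows. Exposure totalled over the hospital stay up to discharge therefore includes perioperative and postoperative drugs, all after allocation. The window closes at discharge rather than at the day-seven assessment, so nothing guarantees that all of the exposure comes before the outcome.

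**Size.** The protocol gives no figure for the effect of rTMS on drug use or of drug use on POCD, so there is no stated figure to reproduce. Inputs:

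- Risk ratio without bias: Sample size {14} assumes 40% incidence and a reduction of 15 percentage points, so (40 - 15)/40 = 25/40 = 0.625.
- d, the shift in opioid burden caused by rTMS, in SD: assumed 0 to -0.4.
- m, the factor by which each SD of opioid burden multiplies POCD risk: assumed 1.2 to 1.5.

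In a log-linear risk model with no interaction and no unmeasured common cause, total RR = direct RR × m^d. Adjusting for the exposure returns the direct RR, so adjusted RR = total RR / m^d.

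- d = 0, any m: m^d = 1, adjusted RR = 0.625.
- d = -0.2, m = 1.2: 1.2^-0.2 = 0.964, and 0.625/0.964 = 0.65.
- d = -0.4, m = 1.5: 1.5^-0.4 = 0.850, and 0.625/0.850 = 0.74.

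**Simulation check.** Each scenario had 400,000 simulated participants and compared the unadjusted risk ratio with that from a log-link Poisson model including opioid burden. All parameters are assumed. In the first four rows each SD of burden adds 0.25 to the log risk; in the last three it has no effect of its own. Control risk was about 34% to 36%.

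| Shift by rTMS (SD) | Unmeasured common cause | Unadjusted RR | Adjusted RR |
|---|---|---|---|
| 0 | No | 0.62 | 0.62 |
| -0.3 | No | 0.64 | 0.69 |
| -0.5 | No | 0.63 | 0.71 |
| -0.5 | Yes | 0.63 | 0.75 |
| -0.5, true RR 1 | Yes | 0.99 | 1.06 |
| -0.3, true RR 1 | Yes | 1.01 | 1.05 |
| 0, true RR 1 | Yes | 1.01 | 1.01 |

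The estimate moves only where rTMS changes the exposure. Where it does, a protective effect is pulled towards 1 in these scenarios, and a null effect can drift away from 1.

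**The case against.** The strongest reply is that bias is possible but not shown. It requires rTMS to change opioid or psychotropic use, and no section says that it does. The protocol also works to keep exposure low: cognition-affecting drugs are prohibited unless indispensable, opioid-sparing strategies are preferred, and planned analgesia rests on femoral nerve blocks with acetaminophen and celecoxib. POCD is classified by a blinded assessor from MoCA items, and nothing says that this result reaches prescribers. All of this stands. It is why the range must include no distortion, and why confidence is high for the textual conflict but not for the presence or size of bias.

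A reader might also infer that the covariates are purely postoperative doses, measured after every rTMS session. The text does not say so. It speaks of total burden captured during hospitalisation and at discharge, and gives no admission date relative to the five sessions, so some exposure could fall within the rTMS course. That exposure would still come after allocation, so the core point is unaffected.

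Finally, the extreme-exposure exclusion is already labelled a sensitivity analysis and is not itself a competing primary analysis. That is fair.

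None of this reconciles the two covariate specifications or turns an exposure arising after allocation into a confounder.

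**Conclusion.** The point holds. The primary model is stated inconsistently between {11d} on one side and {12} and {20a} on the other. The {11d} version adds variables that arise largely after randomisation, on a rationale that does not fit a randomised comparison. Adjusting for them can bias the intention-to-treat risk ratio; it would be too strong to say that it does. Under the assumed inputs, 0.625 would be reported as 0.625 to about 0.74, and the lower end applies if rTMS leaves drug use unchanged. The upper end depends wholly on assumptions that the protocol cannot confirm.

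A reader might also infer that the {12} and {20a} model contains only pre-treatment covariates. It does not. Baseline MoCA is defined there as preoperative day one, which Participant timeline {13} places after completion of the rTMS course. That is a separate matter, but it means that removing the medication terms does not by itself leave a wholly pre-treatment covariate list.

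**What to change.** Before any unblinded analysis:

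1. Delete the {11d} statement that the medication metrics enter the primary models.
2. Use one covariate list for the primary model, the same in {11d}, {12} and {20a}, with no medication exposure.
3. Report opioid and psychotropic exposure by arm descriptively, and label any exposure-adjusted model supplementary.
4. Keep the extreme-exposure exclusion as a sensitivity analysis if wanted, with a note that it selects on a post-randomisation variable.
5. Align the reference to covariate adjustment in the Discussion's limitations.

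Using the preoperative day six MoCA as the covariate would be a further change to {12} and {20a}, to be decided and recorded separately.

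The cost is a few sentences of text across these sections. No new data are needed.
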